#### - Formulation Information

Oral retard pill

#### - Instructions for Use

Nitrofurantoin Uro-Tablinen® pills are taken orally during or after a meal with plenty of liquid.

#### **8.4.1 Selection of dose**

The dose of 100 mg Nitrofurantoin Uro-Tablinen® (retard effect, 50 mg) will be given according to the patients body weight (adapted to patient weight – daily dose 3,6 mg/kg patient weight) and will be then administered two times a day for 5 days.

#### **8.4.2 Potential Toxicity in Patients**

The following safety data of Nitrofurantoin Uro-Tablinen® refer to SmPC Nitrofurantoin Uro-Tablinen® 50 mg, Version June 2019.

#### Tabulated summary of adverse reactions:

The frequency of adverse reactions reflects treatment with Nitrofurantoin 30 mg administered 3 times a day according to EMA. Undesireble effects are stated in table below as rare ( $\geq 1/10,000$  to  $< 1/1,000$ ).

**Table 1: List of adverse drug reactions associated with Nitrofurantoin Uro-Tablinen®**

| System Organ Class                | Preferred term ordered by seriousness                                                                                                                                                                                                                                                                                                     | Frequency |
|-----------------------------------|-------------------------------------------------------------------------------------------------------------------------------------------------------------------------------------------------------------------------------------------------------------------------------------------------------------------------------------------|-----------|
| Infections and parasitic diseases | Super Infections through Pseudomonas- or Candida species (on the urogenital tract limited)                                                                                                                                                                                                                                                | Not known |
| Blood and the lymphatic system    | megaloblast Anemia                                                                                                                                                                                                                                                                                                                        | Not known |
| Blood and the lymphatic system    | Blood count changes (e.g. eosinophilia, thrombocytopenia, agranulocytosis and neutropenia, leucocytopenia, pancytopenia, acute hemolytic anemia)                                                                                                                                                                                          | < 1/10000 |
| Immune system                     | Cutaneous vasculitis                                                                                                                                                                                                                                                                                                                      | Not known |
| Immune system                     | Autoimmune reactions (so-called lupus-like syndromes, "lupus-like syndromes", with symptoms like exanthema, arthralgia, eosinophilia, fever, positive Coombs-Test, antinuclear antibodies, antibodies against smooth muscle or against Glomeruli); anaphylactic/anaphylactoid reactions incl. anaphylactic shock, partly life-threatening | < 1/10000 |
| Immune system                     | Allergic reactions: Drug fever                                                                                                                                                                                                                                                                                                            | ≥1/10     |
| Psychiatric Diseases              | Confusion, depression, euphoria and psychotic Reactions                                                                                                                                                                                                                                                                                   | ≥ 1/10000 |
| Nervous System                    | Increase of intracranial pressure                                                                                                                                                                                                                                                                                                         | Not known |
| Nervous System                    | peripheral polyneuropathies (including optical neuritis) with partly irreversible symptoms muscle weakness, paresthesia and sensibility (hypesthesia, hypothermesthesia), drowsiness                                                                                                                                                      | < 1/10000 |

|                            |                                                                                                                                                                       |           |
|----------------------------|-----------------------------------------------------------------------------------------------------------------------------------------------------------------------|-----------|
| Nervous System             | Headache (especially at the beginning of therapy) as well as dizziness, ataxia, nystagmus                                                                             | ≥1/10     |
| Respiratory System         | Pulmonary reactions: allergic pulmonary edema, pulmonary infiltration ("nitrofurantoin pneumonia"), interstitial pneumonia, pleurisy, dyspnea, cough, and chest pain. | ≥1/100    |
| Respiratory System         | pulmonary fibrosis; asthma attacks                                                                                                                                    | < 1/10000 |
| Gastrointestinal disorders | Especially at the beginning of therapy: gastrointestinal complaints caused by central nervous system (loss of appetite, nausea, vomiting)                             | ≥1/10     |
| Gastrointestinal disorders | Diarrhoe (especially at the beginning of therapy)                                                                                                                     | ≥ 1/10000 |
| Gastrointestinal disorders | pancreatitis; parotitis                                                                                                                                               | < 1/10000 |
| Liver and Bile             | Liver reactions: reversible cholestasis until life-threatening chronically active or granulomatous hepatitis, increase in transaminases                               | ≥ 1/1000  |
| Liver and Bile             | liver necrosis with fatal liver failure, autoimmune Hepatitis                                                                                                         | Not known |
| Skin and subcutaneous      | allergic skin lesions (e.g., exanthema, pruritus, urticaria), angioedema                                                                                              | ≥1/10     |
| Skin and subcutaneous      | Erythema nodosum, erythema multiforme, Stevens-Johnson-syndrome, Lyell's syndrome (sometimes life-threatening), transitory alopecia                                   | < 1/10000 |
| Kidney and urinary tract   | Crystalluria                                                                                                                                                          | < 1/10000 |
| Kidney and urinary tract   | Interstitial Nephritis                                                                                                                                                | Not known |

|                                                                |                                                  |           |
|----------------------------------------------------------------|--------------------------------------------------|-----------|
| Sexual organs and the mammary gland                            | reversible inhibition of spermatogenesis         | < 1/10000 |
| General diseases and complaints at the place of administration | Circulatory collapse                             | < 1/10000 |
| General diseases and complaints at the place of administration | Harmless yellow or brown coloration of the urine | Not known |

**Please note that data on adverse reactions/adverse events may change over the time. For that reason, it is necessary that the investigator is familiar with the current version of the SmPC which is filed in the Investigator site file (ISF).**

#### 8.4.3 Authorization holder of study medication

The authorization holder of the study medication is Winthrop Arzneimittel GmbH. It will be provided by the local pharmacy (ATC code: J01XE01, Nitrofurantoin).

#### 8.4.4 Drug Supply

The pharmacy of the clinic will provide sites with study medication on request by KKS. After the initiation visit, the center will be provided with study medication for patients.

Study medication must be received by designated personnel at the study site. The acknowledgement of receipt has to be sent back to KKS and pharmacy via fax and has to be stored in the ISF. The receipt of medication also has to be documented on the delivery log that is filed in the ISF.

#### 8.4.5 Handling and storage of the medication

The medication has to be handled and stored safely and properly. It has to be kept in a secured location to which only the investigator and designated site personnel have access. The study medication has to be stored below 30°C. The min/max temperature has to be documented in the temperature log found in the ISF. The ready-to-use retard capsules must remain in the outer carton in order to protect the contents from light.

#### 8.4.6 Application of the study medicine

Study medication will be administered only by an authorized person at the investigator's site.

The administration of study medication for each patient has to be documented on the drug accounting form found in the ISF. Destruction of study medication at site can take place only after sponsor approval.

#### **8.4.7 Dose and adjustment of study treatment**

The dose of 100 mg Nitrofurantoin Uro-Tablinen® (retard effect, 50 mg) will be each administered adapted to patient weight (daily dose 3,6 mg/kg patient weight) two times a day over 5 days.

#### **8.4.8 Treatment after termination of study**

The treatment after completion of the clinical trial (premature or regular) is decided individually between investigator and patient.

#### **8.4.9 Management of toxicities of IMP**

Toxicity: 100-120 mg to 2-year-olds did not produce any symptoms. 300 mg to 8 years of age gave moderate intoxication. Benign intracranial pressure increase in a 10-month-old child (75 mg daily for 1 week).

Symptoms: Nausea, vomiting, diarrhea. Headache, dizziness, ataxia, paresthesia, tremor. Pulmonary hypersensitivity reaction, exanthema, urticaria. Hemolytic anemia in predisposed persons. Polyneuropathy in people with renal impairment.

Treatment: If justified gastric emptying, carbon. Provide good diuresis. Alkaline urine speeds up the secretion. Symptomatic treatment. In case of polyneuropathy: treatment with vitamin B6. Liver and renal function should be monitored, as well as a complete blood count should be done.

#### **8.4.10 Reference Document- Nitrofurantoin Uro-Tablinen®**

The current version of the SmPC is kept in the Investigator site file (ISF). In case of changes to the Safety Reference document, SelectImmune Pharma and the coordinating investigator has to re-evaluate the risk-benefit assessment.

#### **8.4.11 Allowed concomitant medication**

1. Increased absorption with food or agents delaying gastric emptying.
2. Decreased absorption with magnesium trisilicate.

3. Decreased renal excretion of Nitrofurantoin by probenecid and sulfinpyrazone.
4. Decreased anti-bacterial activity by carbonic anhydrase inhibitors and urine alkalisation.
5. Anti-bacterial antagonism by quinolone anti-infectives.
6. Interference with some tests for glucose in urine.
7. As Nitrofurantoin belongs to the group of Antibacterials, it will have the following resulting interactions:

- Typhoid Vaccine (oral): Antibacterials inactivate oral typhoid vaccine.

8. In case of anaphylactic reactions: Treatment according to standard treatment guidelines: vasoactive substances (epinephrine, dopamine, norepinephrine, vasopressin), oxygen, volume administration, antihistaminics (histamine H1 receptor antagonists), glucocorticoids

## **8.5 Drug Accountability and Compliance Checks**

### **8.5.1 Drug Accountability Investigational Product**

The investigator is fully responsible for the investigational products at the trial site, for maintaining adequate control of the investigational products, and for documenting all transactions with them.

An inventory (Individual Drug Accountability Form) must be kept tracking the investigational product given to each subject enrolled in the trial. This inventory log must be available during monitoring visits and will be checked by the monitor to ensure correct dispensing of the investigational product.

### **8.5.2 Trial Product Destruction**

The Trial products will be destroyed by the pharmacy of the clinic.

## **9 Statistical Methods**

### **9.1 Determination of Sample Size**

One of the primary objective of the trial is to evaluate the safety and first signs of efficacy of Kineret. No formal sample size calculation evaluating the power of the trial has been performed. However, a consideration regarding the sample size was made as described below.

## 9.2 Definition of Trial Analysis Sets

All subjects enrolled in the trial (i.e. subjects for whom informed consent has been obtained) will be accounted for in the clinical trial report.

A full analysis set will comprise all enrolled subjects who meet the protocol-defined eligibility criteria.

A safety analysis set will be defined by excluding subjects from the full analysis set who either received no treatment with investigational product and/or for whom no post-baseline safety evaluations are available.

The decisions regarding inclusion/exclusion of subjects and/or subject data from the trial analysis sets will be documented in the clinical trial report.

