### 4.3 Subject identification and randomisation of treatment

All enrolled subjects will be randomized 2:1 to two study treatment groups at Visit 1.

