### 5.3 Exclusion Criteria for All Subjects

1. Breastfeeding
2. Signs of pyelonephritis
3. Uncontrolled Diabetes Mellitus
4. Neutropenia ( $<1,5 \times 10^9/L$ )
5. Signs of genital infections (Vaginitis/ cervicitis)
6. Anamnestic exclusion of patients with active severe infections, history of viral hepatitis (only anamnestic exclusion possible, as immediate inclusion in the study is urgently required for this disease pattern. Serological and other blood test results (processing time  $\geq 24$  hours) cannot be waited for).
7. Patients using CYP450 medications (e.g. Warfarin, Phenytoin)
8. Patients using Phenytoin medication
9. Anamnestic exclusion of patients with a history of tuberculosis or active tuberculosis (only anamnestic exclusion possible, as immediate inclusion in the study is urgently required for this disease pattern. Serological blood test results (processing time  $\geq 24$  hours) cannot be waited for)
10. Extragenital conditions, nephrological conditions, urological conditions, urinary catheters that may lead to complicated UTI
11. Severe uncontrolled systemic disease
12. Systemic Antibiotic therapy within 5 days prior to inclusion
13. Impaired renal function (Creatinine clearance  $< 60$  ml /min)

14. Known allergies/contraindications to Kineret and Nitrofurantoin
15. Malign diseases
16. Immunosuppression
17. Previously enrolled in this trial
18. Pathological liver enzymes
19. Polyneuropathies
20. Glucose-6-phosphate dehydrogenase deficiency
21. Participation in other interventional clinical trials
22. Use of Diclofenac and Ibuprofen analgetic medication while participating in this clinical trial

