### 11.4 Protocol violation and discrepancies

Any protocol violation has to be recorded and documented either as "note" in the e-CRF or by using the study specific file notification form, which has to be signed and forwarded to the project manager. In the KKS all protocol violation will be tracked in a separate database. Prior to database soft lock, all protocol violation encountered throughout the study will be reviewed and their consequences on the efficacy evaluation will be assessed.

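### Section 9.2 conditions the full analysis set on eligibility and cuts the safety set out of it, so a dosed patient later judged ineligible is in neither set

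*Protocol*

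**What the plan says.** Protocol section 9.2 defines two analysis sets.

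- **Full analysis set:** "A full analysis set will comprise all enrolled subjects who meet the protocol-defined eligibility criteria". The same section glosses enrolled as "subjects for whom informed consent has been obtained". Neither randomisation nor treatment enters the definition.
- **Safety set:** "A safety analysis set will be defined by excluding subjects from the full analysis set who either received no treatment with investigational product", and also those "for whom no post-baseline safety evaluations are available". It is therefore a subset of the full analysis set.

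These other sections bear on the point:

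- Section 4.3: "All enrolled subjects will be randomized 2:1 to two study treatment groups at Visit 1".
- Section 4.3.2 allows randomisation only once every eligibility criterion is satisfied.
- Sections 6.1 and 6.2 put the eligibility check, blood sampling, randomisation and first dispensing of study drug all at Visit 1, Day 1.
- Section 5.3, exclusion 22: "Use of Diclofenac and Ibuprofen analgetic medication while participating in this clinical trial".
- Section 11.4 provides that before soft lock "all protocol violation encountered throughout the study will be reviewed and their consequences on the efficacy evaluation will be assessed".

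**The concern.** Eligibility found wanting after randomisation is a reason to describe a patient, and perhaps to run a sensitivity analysis without her. It is not a reason to remove her from the main efficacy set, because removal after allocation gives up the comparability that randomisation created. It is still less a reason to remove her from the safety set once she has received the drug. Sections 9.1 and 9.3 both name safety as part of the primary objective, so the safety denominator should be everyone exposed.

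The trial is open label and has 30 patients. Any judgement on eligibility after entry is made with the arm known, and each such judgement moves a visible share of the data.

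Exclusion 22 adds a second route. The primary endpoint is the reduction in ACSS symptom score over the first 5 days (section 3.2.1), and section 2.1 acknowledges that NSAIDs can help acute symptoms. If taking ibuprofen during the trial counts as failing eligibility, membership of the efficacy set could depend on behaviour related to the endpoint.

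**Working it through.** The main result is set logic; the arithmetic only gives scale. The protocol states no figure of its own here to reproduce.

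**Step 1: follow one patient through section 9.2.** Take a woman who consented, was randomised and received a dose, and is afterwards found to breach an exclusion criterion.

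- Full analysis set = consented AND eligible. She is consented but not eligible, so she is out.
- Safety set = full analysis set, minus the untreated, minus those with no post-baseline safety evaluation. She is not in the starting set, so she is out, although she was treated.
- No other section puts her back into either set.

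**Step 2: can this happen?** The blood count with differential and the creatinine are in the section 6.10.1 panel and are drawn at Visit 1, the day of randomisation and first dosing. Neutropenia (exclusion 4) and creatinine clearance below 60 ml/min (exclusion 13) depend on those results. The protocol does not say when they are available. Late discovery is possible; its frequency is not stated.

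**Step 3: size of one exclusion.** Section 4.2 gives 20 Kineret and 10 nitrofurantoin patients.

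- Kineret: 1/20 = 5% of the arm.
- Control: 1/10 = 10% of the arm.

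**Step 4: effect on a safety table (constructed example).** Suppose one Kineret patient has the only event and is later judged ineligible.

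- All treated: 1/20 = 5.0%, exact 95% CI 0.1% to 24.9%.
- As section 9.2 is written: 0/19 = 0%, exact two-sided 95% upper limit 1 − 0.025^(1/19) = 17.6%.

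The loss of precision alone is small: with no events, the same limit is 1 − 0.025^(1/20) = 16.8% at n = 20 against 17.6% at n = 19. What matters is which patient is removed.

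**Step 5: chance that at least one of 30 is affected.** The formula is 1 − (1 − q)^30, where q is an assumed ineligibility rate that does not come from the protocol.

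| Assumed q | Expected number, 30q | Chance of at least one |
|---|---|---|
| 2% | 0.6 | 45% |
| 5% | 1.5 | 79% |
| 10% | 3.0 | 96% |

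**Step 6: the post-baseline condition.** A dosed patient with no later safety evaluation contributes no recorded event, so removing her shrinks only the denominator. With one event among the others, the rate goes from 1/20 = 5.0% to 1/19 = 5.3%. This condition does not hide events, but it does make the safety set something other than all exposed patients.

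**The case against.** The strongest reply is that eligibility is checked at Visit 1 only and must be satisfied before randomisation, so few or no ineligible patients should be randomised. That is the intended process, and it limits how often the problem arises. It does not say what happens when a breach is found later, and there section 9.2 gives the wrong answer.

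A reader might infer several stronger claims that the protocol does not support.

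- **That ibuprofen users will drop out of the efficacy set.** On the ordinary reading, eligibility is judged at entry and later NSAID use is a protocol violation under section 11.4. Removal is one possible reading of exclusion 22. Nothing in the protocol shows that such use would differ by arm, and section 6.2 keeps treatment failures in the study.
- **That laboratory exclusions will routinely surface after dosing.** The statement that results cannot be awaited belongs to exclusions 6 and 9 (severe infection or hepatitis, and tuberculosis), not to neutropenia or creatinine clearance. Liver enzymes are not in the section 6.10.1 panel, so that sample could not reveal a breach of exclusion 18.
- **That harms go unrecorded.** Section 9.2 accounts for all consented subjects in the report, and sections 7.1 and 7.3 collect AEs and SAEs from consent to 30 days after the last dose, whatever the analysis set.
- **That exclusions are documented only in the report.** Section 11.4 has violations recorded, tracked in a database and reviewed before soft lock.
- **That never-randomised patients will populate the full analysis set.** Section 4.3 says all enrolled subjects are randomised. The two uses of enrolled need reconciling, but no bias is shown.

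The statistical analysis plan is not at hand and might redefine the sets. The protocol nevertheless fixes them itself, and section 9.3.2 requires changes from the planned analysis to be described and justified, so this is not a matter merely left open.

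**Conclusion.** The point holds as a defect in the written definitions. A randomised and dosed patient later judged ineligible is outside both analysis sets, and no other section corrects this. Each such patient is 5% of the Kineret arm or 10% of the control arm; the change from 1/20 to 0/19 is illustrative. The number affected is unknown, and the rates of 2% to 10% used above are assumptions.

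It may be tempting to say that the patients most at risk of harm are the ones removed. Renal impairment and neutropenia are exclusions, section 2.2 says Kineret is cleared mainly by the kidneys, and neutropenia is a listed reaction in section 8.2.2, so this is plausible. It remains an inference, because the protocol does not show that such patients would be dosed. Exclusion 22 is an ambiguity to close, not a demonstrated bias.

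**What to change.** Rewrite section 9.2, and carry the same definitions into the statistical analysis plan:

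1. **Full analysis set:** all randomised patients, analysed in the arm to which they were randomised.
2. **Safety set:** all patients who received at least one dose, analysed by treatment received. Define it independently of the full analysis set, with no eligibility or post-baseline condition.
3. **Per-protocol sensitivity set:** deal with eligibility violations and diclofenac or ibuprofen use here, with membership rules fixed in writing before outcomes by arm are reviewed.
4. State whether exclusion 22 is judged at entry or throughout participation, and that use after randomisation does not affect membership of the full analysis set. Use enrolled in one sense in sections 4.3 and 9.2.

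The cost is wording only: no extra patients, visits or data. The full analysis set may include a few ineligible patients, which would dilute the efficacy estimate slightly; the sensitivity set shows by how much.
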